# TargetCOPD: a pragmatic randomised controlled trial of targeted case finding for COPD *versus* routine practice in primary care: protocol

**DOI:** 10.1186/1471-2466-14-157

**Published:** 2014-10-04

**Keywords:** COPD, Case-finding, Screening, Primary care, Respiratory questionnaire, Spirometry, Cluster RCT, Cost-effectiveness

## Abstract

**Background:**

Many people with clinically significant chronic obstructive pulmonary disease (COPD) remain undiagnosed worldwide. There are a number of small studies which have examined possible methods of case finding through primary care, but no large RCTs that have adequately assessed the most cost-effective approach.

**Methods/Design:**

In this study, using a cluster randomised controlled trial (RCT) in 56 general practices in the West Midlands, we plan to investigate the effectiveness and cost-effectiveness of a Targeted approach to case finding for COPD compared with routine practice. Using an individual patient RCT nested in the Targeted arm, we plan also to compare the effectiveness and cost-effectiveness of Active case finding using a postal questionnaire (with supplementary opportunistic questionnaires), and Opportunistic-only case finding during routine surgery consultations.

All ever-smoking patients aged 40-79 years, without a current diagnosis of COPD and registered with participating practices will be eligible. Patients in the Targeted arm who report positive respiratory symptoms (chronic cough or phlegm, wheeze or dyspnoea) using a brief questionnaire will be invited for further spirometric assessment to ascertain whether they have COPD or not. Post-bronchodilator spirometry will be conducted to ATS standards using an Easy One spirometer by trained research assistants.

The primary outcomes will be new cases of COPD and cost per new case identified, comparing targeted case finding with routine care, and two types of targeted case finding (active *versus* opportunistic). A multilevel logistic regression model will be used to model the probability of detecting a new case of COPD for each treatment arm, with clustering of patients (by practice and household) accounted for using a multi-level structure.

A trial-based analysis will be undertaken using costs and outcomes collected during the trial. Secondary outcomes include the feasibility, efficiency, long-term cost-effectiveness, patient and primary care staff views of each approach.

**Discussion:**

This will be the largest RCT of its kind, and should inform how best to identify undiagnosed patients with COPD in the UK and other similar healthcare systems. Sensitivity analyses will help local policy-makers decide which sub-groups of the population to target first.

**Trial registration:**

Current controlled trials ISRCTN14930255

**Electronic supplementary material:**

The online version of this article (doi:10.1186/1471-2466-14-157) contains supplementary material, which is available to authorized users.

## Background

Chronic obstructive pulmonary disease (COPD) affects 5-10% of adults worldwide [1], is rising in prevalence [2], and is a leading cause of death [3]. In the UK it accounts for 1.4 million GP consultations, 1 million in-patient days per year and costs the NHS over £800 million per year [4]. However, around 45-85% of cases [5–7], depending on diagnostic criteria, remain undiagnosed, representing many with potentially unmet need. There is much uncertainty about how to approach early identification of patients [8, 9], although it has been recently demonstrated that there are many missed opportunities to diagnose patients in primary care where signs and symptoms have been overlooked [10].

The CMO's report, 2005 [11] and the Healthcare Commission report [12] highlighted the burden of COPD, the extent of under-diagnosis and variation in access to relevant services. As a result a National Clinical Outcomes Strategy has been published recommending case finding in high risk patients [13], resulting in a British Lung Foundation campaign [14] and drive to identify missing cases [15, 16]. Several NHS Trusts have started initiatives [17, 18].

Despite the move towards early case-finding for COPD, the most effective and cost-effective approach is not known. There are no relevant published systematic reviews, though many small pre-post studies have reported on approaches to case finding. These report either active [5, 19, 20] or opportunistic [21–24] approaches (with yield 18-47%), but are limited because of a lack of comparison groups, restricted number and range of participants, incomplete follow up or different target populations. More recently a few trials have been published. A small trial from a single practice reported a higher prevalence of airflow obstruction with an opportunistic compared to invitation based approach to case finding [25]. The population however was highly deprived, with many non-English speakers, and no economic analysis was undertaken. A cluster RCT in 16 general practices in the Netherlands which used an initial screening questionnaire to identify patients at risk found that a practice-managed approach to calculating the score and inviting patients for spirometry assessment was more effective than a patient-led approach of applying for spirometry assessment having calculated their own scores [26]. Additionally, we have also reported a pilot study in two general practices which suggested that it may be more cost-effective to undertake opportunistic screening; however the study was underpowered and the results require proper testing in a full RCT [27]. The limitation of the current evidence base and lack of adequate data from RCTs contributed to the recent recommendation by the UK National Screening Committee against screening for COPD [28], and justifies a new adequately-powered trial.

Many studies have used spirometry alone to screen for COPD. However this is not recommended [8] as it would identify many without clinically important disease for whom there is little evidence of effective interventions [29, 30]. National Institute for Clinical Excellence (NICE) guidelines recommend opportunistic case finding in those presenting with relevant symptoms and exposures (mainly smoking) [31]. Our analysis of the Health Survey for England (HSE), a large dataset representative of the English population, shows that targeted case-finding among smokers aged ≥40 with relevant symptoms would have greater yield than targeting the general population [32]. Of the undiagnosed cases likely to be detected, more than three quarters could benefit from evidence based treatment (e.g. pulmonary rehab, inhaled therapies, vaccination & smoking cessation interventions), and there is new evidence that others may also benefit [33]. Modelling of data from the Health Survey for England indicated that active case-finding (with postal questionnaire plus opportunistic case-finding in primary care consultations) would be more effective than opportunistic case-finding alone, but this needs empirical testing [32].

Cases identified are expected to benefit from treatment resulting in improved quality of life, increased survival, reduction in hospital admissions and less work-related absence. Published economic evaluations in COPD have primarily considered interventions for the disease rather than diagnosis, and others have concentrated on the costs of COPD in burden of illness studies. No trial-based economic evaluation has considered case-finding. NICE guidelines included simple decision-tree based modelling to determine the cost-effectiveness of opportunistic case finding among ever smokers over 35 years old with chronic cough [31]. The model is simplistic, contains many assumptions and requires better data on the natural history of the disease. The proposed cost-effectiveness component of this study will resolve this issue.

In this study, using a cluster RCT in general practices across the West Midlands, we plan to investigate the effectiveness and cost-effectiveness of a Targeted approach to case finding for COPD compared with routine practice. Using an individual patient RCT nested in the targeted arm, we plan also to compare the effectiveness and cost-effectiveness of Active case finding using a postal questionnaire (with supplementary opportunistic questionnaires), and Opportunistic case finding at routine surgery consultations.

## Methods

### Aims and objectives

To determine whether Targeted case finding is more effective and cost-effective than routine practice.To evaluate the relative effectiveness and cost-effectiveness of two alternative methods of targeted case finding: Active (postal questionnaire plus flagging of patient records) versus Opportunistic (flagging only).

### Design

TargetCOPD is a pragmatic randomised controlled trial of a case-finding intervention, delivered at organisational level, with two elements (Figure 1):

**Figure 1 Fig1:**
[figure not shown]
**Plan of trial including projected numbers**
[32]
**.**

Cluster randomised trial comparing Targeted case finding (28 practices) with routine practice (28 practices).Individually randomized controlled trial nested within the targeted case finding arm comparing two alternative types of targeting: Active (A) versus Opportunistic (O).

### Setting

Fifty six general practices in the West Midlands will be recruited through the Primary Care Research Network for Central England (PCRN-CE) at the University of Birmingham.

### Participants

Patients will be identified as eligible if they are:

registered at a participating practiceaged between 40 and 79 years (inclusive) on the date of the record search,identified as current or ex-smokers according to their patient recordshave no prior diagnosis of COPD

Automated computer searches will be used for identifying all eligible patients using READ codes (Additional file 1: Appendix 1). Patients will be further assessed for eligibility to take part in assessments by their GP and those not considered suitable will not be invited for assessment (e.g. if unable to give informed consent, suffering from a terminal illness or pregnant).

### Intervention

All interventions will take place over one year. The schema is given in Figure 1 with projected patient numbers. Fifty six practices will initially be randomised to continue with routine care or to a targeted approach to case finding.

#### Routine practice arm

In the routine practice arm of the cluster trial, practices will continue with their usual care and new cases of COPD will be identified according to usual practice. NICE guidance recommends that patients over the age of 35 years should be investigated for COPD with spirometry if they present opportunistically with chronic cough or phlegm [31].

#### Targeted case finding arm

Within the targeted arm of the cluster trial, participants will be randomly allocated (by household) to receive either the Opportunistic or the Active case finding intervention:

#### Stage 1: respiratory questionnaire

##### Opportunistic

Patients in this arm will have their records flagged to prompt the consulting healthcare practitioner or receptionist to provide them with a brief screening questionnaire consisting of simple respiratory questions supplemented with basic socio-demographic and medical information (Additional file 1: Appendix 2). The questionnaire is based on validated questions, where available, and has been piloted. Patients who agree to take part will leave the questionnaire with the receptionist.

##### Active

In addition to having their records flagged to allow opportunistic provision of the questionnaire, eligible patients in the Active arm will also be sent a postal questionnaire (with reply-paid envelope). If the questionnaire has not been received within four weeks after posting, then a first reminder will be sent. After a further four weeks, a second reminder will be sent. (It has been shown that the response rate to respiratory questionnaires is maximized with two reminders) [34].

Once the questionnaire has been returned to the investigators, the computer flag will be removed.

#### Stage 2: spirometry assessment

Any patient responding positively to the respiratory symptom questions (chronic cough or phlegm for three or more months of the year for two or more years, wheeze in the last 12 months or dyspnoea of MRC grade 2 or more) will be invited to attend for spirometry to ascertain whether they have COPD or not.

This will take place in a room at the patient’s GP practice or an alternative local venue. Post-bronchodilator spirometry will be undertaken according to ATS/ERS 2005 guidelines [35] and carried out by research assistants trained to high standards using a short modified programme modelled on the ARTP Spirometry course by the lung function unit at Queen Elizabeth Hospital Birmingham. The research assistants will undertake frequent refresher training and monitoring of quality throughout the trial. FEV_1_, FVC, FEV_6_ will be measured using the Easy One spirometer (ndd, Switzerland). Patients will be administered 400 micrograms salbutamol through a spacer, and asked to rest for 20 minutes prior to undergoing spirometry. Customised software ([name]) will be used to ensure real-time quality of each manoeuvre and every trace over-read.

All spirometry results will be provided to their GP.

During the assessment visit, patients will also be asked to complete a short questionnaire to ascertain their out of pocket expenses for attendance (Additional file 1: Appendix 3), health status (EQ-5D) [36], job type (using CASCOT software) and the COPD Assessment Test. [37] Patients’ height will be measured to the nearest cm using a portable stadiometer (or estimated using arm-span if necessary), and weight (to the nearest 0.1 kg) will also be measured using GP scales by trained researchers.

### Allocation to trial arm

#### Cluster randomised trial comparing targeted case finding with routine care

Recruited practices will be allocated into intervention arms using block randomization. Ideally block size will be at least eight practices [38, 39], with an equal number of practices allocated to intervention and control groups by the end of each block.

A minimization algorithm will be used to allocate practices to intervention groups to ensure balance across the groups for the following covariates: deprivation, ethnicity, practice size, age and proportion of COPD patients on the Quality and Outcomes Framework (QOF) COPD register [40]. Any linked practices (those practices that have the same GPs across two sites, each with a different patient list) will be stratified so that the allocation to trial arm will be the same in order to avoid contamination. The algorithm generates an ordered list of the possible permutations of randomization within each block – at the top of the list are the permutations which minimize imbalance the best. Of those at the top of the list (e.g. the top 10%), one will be chosen at random to use.

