### Statistical justification for sample size

As there are two primary outcomes, the significance level for multiple testing is adjusted so that in total (across both sample size calculations) there is a 5% significance level. The individually randomised component (outcome (b) below) comparing Active versus Opportunistic case finding requires far fewer patients for adequate power and is therefore given 0.25% significance level. The cluster component (a) is designated 4.75% significance level.

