#### (a) Targeted case finding versus Routine care cluster randomized design

Based on the authors’ modelling work [32], the proportion of new COPD cases detected in the Targeted group (averaged across both Active and Opportunistic arms) was assumed to be 3.15%. Based research by Simpson et al. [42], the proportion of new COPD cases detected in the Routine care group was assumed to be 0.75%. At the 4.75% significance level, with 80% power, this led to an unadjusted sample size required of 545 per group, in order to detect a difference of 2.4% between Targeted and Routine care arms.

We expect ~40% of a practice population to be age 40-79 yrs with 57% of these being ever smokers without a previous diagnosis of COPD [32]. Assuming therefore a conservative 1000 eligible patients per practice of average list size 6000, and adjusting for clustering of patients within practices, assuming a conservative ICC of 0.05 [43, 44] the sample size required was 27,768 per arm, equivalent to 28 practices per arm.

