#### Targeted case finding vs Routine care (cluster design)

Baseline characteristics of patients and uptake rate at each stage will be described for each cluster, and compared across clusters to check for balance across groups. A multilevel logistic regression model will be used to model the probability of detecting a new case of COPD in the Targeted group compared with the Routine care group. Clustering of patients (by practice and household) will be accounted for using a multi-level structure. The data will also be modelled using a log-link and results from the logit-link and log-link models will be compared. OR and also RR and risk differences will be estimated [45, 46], as will the NNT (Number Needed to Target to identify one additional COPD case). The analysis will also adjust for variables used in the randomization (age, ethnicity, deprivation) which might affect probability of having COPD.

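### Linked practices are randomised together, but the Targeted-versus-Routine model names practice as its highest cluster; if linked practices are enrolled and coded separately, its standard error will be somewhat too small

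*Protocol article*

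**What the plan says.** All references are to the Protocol article.

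- **Allocation to trial arm, cluster randomised trial.** Linked practices are defined as "those practices that have the same GPs across two sites, each with a different patient list". They "will be stratified so that the allocation to trial arm will be the same in order to avoid contamination". The text does not say how many linked practices are expected or were recruited.
- **Primary analyses, Targeted case finding vs Routine care.** "Clustering of patients (by practice and household) will be accounted for using a multi-level structure". No level above practice is named. The covariates listed in brackets are age, ethnicity and deprivation.
- **Secondary analyses.** The only further work on clustering is a sensitivity analysis at household level.
- **Statistical justification for sample size.** "The cluster component (a) is designated 4.75% significance level". In part (a), with 1000 eligible patients per practice and an ICC of 0.05, "the sample size required was 27,768 per arm, equivalent to 28 practices per arm".

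**The concern.** A cluster trial should be analysed with its highest level at or above the unit that was randomised. Here a single random choice fixes the arm of both sites in a linked pair, while the stated model stops at practice. The allocation section calls each linked site a practice with its own list, so on a plain reading a pair enters the model as two independent clusters.

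The article treats the parallel case differently. Households are also allocated jointly to avoid contamination, and household does appear as a clustering level.

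Positive correlation within a pair is plausible. In the Routine arm, new cases arise only through usual care by the shared GPs. In the Targeted arm, the practice's own staff are prompted to hand out questionnaires. If the correlation is present and ignored, the standard error of the Targeted-versus-Routine comparison is understated, its type I error exceeds the allotted 4.75%, and the effective number of clusters behind the 80% power is overstated.

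**Working it through.** **1. Reproduce the plan's figure.** Inputs from part (a) of the sample size section: 3.15% v 0.75%, alpha 4.75% (taken as two-sided, since the sidedness is not stated), power 80%, 1000 eligible patients per practice, ICC 0.05.

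- A pooled two-proportion formula without continuity correction gives 529 per group, against the stated 545 (2.9% lower).
- Design effect = 1 + (1000 − 1) × 0.05 = 50.95.
- 545 × 50.95 = 27,767.75, which rounds up to the stated 27,768. That is 27.8 practices, so 28 per arm.
- With 28 practices, the effective size is 28,000 / 50.95 = 549.6 per arm, and power is 81.6%.

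The plan's figure holds, with little slack: 27.8 practices needed, 28 planned.

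**2. Where the variance lies.** The between-practice share of the variance of a practice's observed rate is 0.05 / (0.05 + 0.95/1000) = 0.981. A shared GP effect would therefore act on nearly all of the variance that matters.

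**3. Effect of linked pairs.** Let each arm have k = 28 practices, of which L pairs are linked, with correlation ρ between the two practice-level rates in a pair. Neither L nor ρ is in the document; both are assumptions.

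- The true variance of an arm mean is multiplied by V = 1 + 2Lρ/k.
- The variance estimated by treating all practices as independent is itself multiplied by S = 1 − 2Lρ/(k(k − 1)), a second-order effect.
- True SE / model SE is √V, or √(V/S) with the second-order term.
- Actual type I error = 2 × [1 − Φ(1.982/√V)], or with √(V/S) in place of √V.
- Power uses an effective size of 549.6/V per arm. Practices needed per arm = 27.77 × V.

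| L per arm | ρ | V | √V | Type I error | With S | Power | Practices needed per arm |
|---|---|---|---|---|---|---|---|
| 0 | – | 1.000 | 1.000 | 4.75% | 4.75% | 81.6% | 27.8 |
| 1 | 0.5 | 1.036 | 1.018 | 5.15% | 5.16% | 80.2% | 28.8 |
| 1 | 1 | 1.071 | 1.035 | 5.55% | 5.59% | 78.8% | 29.8 |
| 2 | 0.5 | 1.071 | 1.035 | 5.55% | 5.59% | 78.8% | 29.8 |
| 2 | 1 | 1.143 | 1.069 | 6.38% | 6.45% | 76.2% | 31.7 |
| 3 | 0.5 | 1.107 | 1.052 | 5.96% | 6.01% | 77.5% | 30.7 |
| 3 | 1 | 1.214 | 1.102 | 7.21% | 7.32% | 73.6% | 33.7 |

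**4. Check by simulation.** 100,000 runs of practice-level means, compared by a t test on 54 degrees of freedom, gave type I errors of 5.1% (L = 1, ρ = 0.5), 5.5% (1, 1), 6.1% (3, 0.5) and 7.4% (3, 1), in line with the table. Both the formula and the simulation approximate the multilevel logistic model by an analysis of practice-level rates with equal cluster sizes.

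**The case against.** A reader might infer that the primary standard error simply *is* too small. The document does not support that. It is silent on whether any linked practice was recruited, so the number may be zero and the error nil. Nor does it say that a linked pair receives two identifiers; an analyst could code the pair as one practice. Coding of this kind is often settled in a statistical analysis plan, and that plan is not shown.

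Full correlation within a pair is also not established. Linked practices have separate patient lists, so case mix can differ. In the Targeted arm, research assistants perform the spirometry, receptionists may hand out questionnaires, and the Active half also receives them by post. Adjustment for age, ethnicity and deprivation may remove part of any correlation. With one pair per arm at correlation 0.5, power stays at 80.2%. The article calls its ICC conservative: at a true ICC of about 0.041 (0.05/1.214), even three fully correlated pairs per arm would cost no power against the plan. That argument does not touch type I error.

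Finally, the allocation also balances on practice size and the proportion of patients on the COPD register, neither of which is in the bracketed adjustment list. If those factors are prognostic, leaving them out makes the model's standard error too large, which works against the error described here.

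These objections make the harm conditional and its net size uncertain. They do not remove the mismatch. The article does state its clustering levels, and as written they stop below the unit randomised. Balancing on other factors is a separate effect and no reason to leave the cluster wrongly defined.

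**Conclusion.** The point holds as a conditional one, with moderate confidence. The linked set is the randomised unit, and the stated top level of the Targeted-versus-Routine model is practice. Three conditions are needed for harm: linked practices are enrolled, they are coded separately, and their detection rates remain positively correlated after adjustment.

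Under the assumed 1 to 3 pairs per arm and correlation 0.5 to 1, the true standard error is about 2% to 10% above the modelled one. Type I error is about 5.2% to 7.2% (7.3% with the second-order term) instead of 4.75%. Power at the planned ICC is about 80% to 74%. The upper ends rest on fully shared practice effects and are bounds for those pair counts, not expectations. With no linked pairs there is no effect, and balancing on unadjusted factors could offset part of it. A claim that type I error definitely exceeds 4.75% would go beyond the document.

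**What to change.** In the Targeted-versus-Routine model, and in any resampling done at practice level, define the top-level cluster as the unit randomised, so that linked practices share one cluster identifier. Report the number of randomised units per arm beside the number of practices.

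This takes one sentence and a recoded identifier. It changes nothing if no linked practices are enrolled. If some are, the intervals widen slightly and the analysis matches the allocation.
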